## IV - 4 - RECRUITMENT METHOD

Patient recruitment is always difficult for this type of trial. The local/regional recruitment strategies have proven to be effective, particularly in the randomised Thermarthrose trial, a large-scale, randomised, pragmatic trial which included around 400 patients (Forestier R, ARD 2009). This type of recruitment has a logistical advantage as the patients live close to the spa centre and can go home after the intervention. It is therefore not necessary to provide accommodation for them, which has significant advantages in terms of cost and logistical organisation.

Another recruitment method that has proven to be effective is that of networks of general practitioners and specialists in the context of assessment of a Vichy spa therapy programme (Nguyen M, Br J Rheumatol 1997).

A triple recruitment method will be organised:

1. Local recruitment in the regions of Île de France, Auvergne, Languedoc-Roussillon and Rhône-Alpes, informing the patients through local media and posters in pharmacies and waiting rooms of general practitioners and specialists. The information will refer to lower back pain, but not to the short spa therapy programme. All patients that may be interested will be invited to contact a management centre, who will confirm the eligibility criteria, provide the patient with information and refer the patient to an enrolment visit. The enrolment visit will be carried out by a specially trained physician from a centre independent of the spa therapy centre. This method has already proven to be effective in trials in the area of spa therapy (Forestier R, ARD 2009).
2. Recruitment through sick-leave agents from the Assistance Publique in these four regions, and employees from the Michelin group in the region of Auvergne.
3. A more traditional patient recruitment method at the time of consultation, through the same local networks of general practitioners and rheumatologists agreeing to participate actively in this study.

# V – STUDY TREATMENT

## V - 1 – Intensive spa THERAPY

Standardisation of the intervention

A steering committee made up of rehabilitators, spa therapy physicians, rheumatologists, physiotherapists and psychotherapists from the various research sites and spa centres will be responsible for the preparation and standardisation of the intervention. This prior standardisation is essential to ensuring good reproducibility of the intervention during the study and the transfer of the intervention into routine clinical practice, if the trial demonstrates its efficacy.

Two meetings will be organised with all members of the steering committee to obtain a consensus on a therapeutic protocol, precisely describing the content and organisation of the intervention, taking into account the context and expertise of the various sites involved in the study.

Therapists

The various therapists responsible for the implementation of the intervention in this study will have a minimum of 5 years’ clinical experience. They will receive precise training in a specific meeting for the implementation of the intervention and they will receive a detailed manual describing the intervention and videos of each part of the intervention.

Content of the intervention

The patients in the intervention group will receive an intensive spa therapy consisting of the following, on a daily basis for five days:

- 2 hours of spa therapy (morning);
- 30 minutes of physical exercises (afternoon);
- 45 minutes of group therapeutic education (afternoon): two sessions dedicated to physical activity and rest (one of which with a CD), two sessions dedicated to work (one of which with a CD) and one pain-management session using a CD (45 minutes, all in the afternoon).

They will also receive a guide on lower back pain.

Treatment adherence assessment

Quantitative adherence (number and duration of sessions) and qualitative adherence (type of follow-up intervention, and method of performing the intervention) will be systematically assessed.

Tools for the future transfer of the intervention into routine clinical practice

The tools used for training the therapists and standardisation of the intervention before the start of the study will eventually be made available to clinicians for the intervention to be transferred into routine clinical practice. In particular, the intervention will be described in detail in a manual, and each part of the intervention (i.e., the exercise programme and therapeutic education) will be filmed.

Comparator

The patients in the control group will receive standard treatment with no restrictions, organised by their referring physicians, general practitioners or specialists, as well as the same guide on lower back pain given to the intervention group.

## V - 2 – ASSOCIATED TREATMENTS

The prescription of medicinal products such as analgesics and NSAIDs will be left to the investigator’s discretion. There are no prohibited treatments. Any treatment taken or likely to be taken by the patient during the study must be reported in the form of a diary, which will be given to the patient at the enrolment visit.

# VI – ENDPOINTS

## VI - 1 - PRIMARY ENDPOINT

The primary endpoint will be the return-to-work rate at 1 year. A higher return-to-work rate in the intervention arm would allow us to justify the cost of the intervention.

## VI - 2 - SECONDARY ENDPOINTS

The secondary endpoints will be as follows:

- Area under the curve of pain over the past 48 hours, assessed every fortnight using a numeric scale from 0 to 100 at 1 year;
- Functional assessment at 1 year (Quebec scale);
- Quality of Life assessment at 1 year (MOS SF-12 questionnaire);
- TWIST at 1 year (pain);
- Number of days of sick leave between 6 months and 1 year after enrolment. We have not taken into account the total number of days of sick leave as, by definition, the intervention requires the patients to be available for the duration of the treatment, which will involve sick leave.

# VII – PATIENT STUDY PLAN

## VII - 1 – D0 - ENROLMENT VISIT

Patients who may be eligible for enrolment will be referred to the Department of Physical Medicine and Rehabilitation at Cochin, Clermont-Ferrand, Montpellier or Nancy, or else to an independent assessor in Aix les Bains or Dax, in order to be enrolled in the study.

The investigator will systematically confirm the inclusion and exclusion criteria at the enrolment visit. First of all, the investigator will clearly explain to the patient the implications of participating in a cohort study with follow-up by post or email at Months 3, 6 and 12 and a pain assessment by phone every fortnight for 1 year. The patients will also be systematically informed that, for scientific reasons, they will not be given details of any of the research hypotheses until the end of the study. At the end of the study, the patients in the control group will not be able to benefit from the study results. After 1 year of follow-up, patients in the control group who are still on sick leave will no longer justify this type of intervention. If the patient agrees to participate in the cohort study, he or she will sign the initial informed consent form (ICF1).

After signing ICF1, the patients will be randomised using secure computerised randomisation software. The patients randomised into the short spa therapy programme will be offered the treatment and, if they accept, they will sign the second informed consent form (ICF2). For these patients, an enrolment form will be sent by fax to the spa therapy centre of reference, to the Clinical Research Unit (URC) and to the French Association for Spa Therapy Research (AFRETH) to plan the organisation of this treatment.

The following information will be collected in the case report form:

- - Patient contact details (surname, first name, address, email, telephone number(s));
  - Demographic parameters (age, sex);
  - Socioprofessional parameters (level of studies, profession and start date of sick leave);
  - Clinical parameters regarding the lower back pain (date of diagnosis of lower back pain, date of onset of current episode and main aetiology);
  - Assessment of pain over the past 48 hours, assessed using a numeric scale from 0 to 100;
  - Previous and ongoing treatment for lower back pain;
  - Functional indices: Quebec scale;
  - Anxiety/Depression: HAD questionnaire;
  - Quality of Life: MOS SF-12 questionnaire;
  - Fear-avoidance beliefs: FABQ questionnaire;
  - Coping strategies: CSQ questionnaire.

Following this visit, the investigator will give the Month 3, 6 and 12 follow-up self-assessment questionnaires which the patient must fill in and return by mail, from the enrolment visit for the control group and from the end of spa therapy for the intervention group.

Patients randomised into the standardised spa therapy arm will receive a start date for the intervention from the secretary at the spa therapy centre, taking into account a maximum time period of 3 months between the enrolment visit and the therapy. The planning of the stay and patient welcome will be arranged by the spa therapy centre, the choice of accommodation will be managed by the French Association for Spa Therapy Research (AFRETH) and transport passes will be managed by the Clinical Research Unit (URC).

Finally, the investigator will provide the patients with the guide on lower back pain, the patient diary containing the self-assessment questionnaires for the various evaluations, as well as the patient card mentioning the patient’s participation in the study.

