| **Study treatment** | Short, standardised spa therapy (5 days). |
| **Study progress** | One enrolment visit, followed by the intervention protocol for patients in the “standardised spa therapy” arm, then follow-up by mail at Month 3, 6 and 12.  D0 - Enrolment visit and randomisation   - Medical examination - Verification of eligibility criteria - Proposal of cohort study and collection of signed informed consent form - Enrolment - Patient contact information (name and surname, email, phone number) - Demographic information (age, sex) - Socioprofessional information (level of studies and profession) - Date sick leave started - Clinical information regarding lower back pain - Previous and ongoing treatment for lower back pain - Numeric pain scale - Quebec questionnaire - HAD questionnaire - Quality of Life, assessed with: MOS SF12 - FABQ questionnaire - CSQ questionnaire - Randomisation - Proposal of therapy for patients randomised into the intervention group and collection of signed informed consent form   Intervention protocol for patients randomised into the “spa therapy” arm   - Duration: five days, consisting of spa therapy sessions (exercises and hydrotherapy) and group therapy education   Assessments at Months 3, 6 and 12   - By post or email, together with a phone call if no response is received - Professional status/Return to work - Sick leave periods since the previous visit - Numeric pain scale - Lower back pain progress - Treatment since the previous visit - Adverse events collected - Quebec questionnaire - HAD questionnaire - MOS SF-12 questionnaire - FABQ questionnaire (only at the Month 12 assessment) - CSQ questionnaire (only at the Month 12 assessment) - Treatment satisfaction at 12 months   Pain assessment every fortnight  Numeric pain scale via telephone (IVR system) |
| **Primary and secondary**  **endpoints** | Primary endpoint  The primary endpoint will be the return-to-work rate at 1 year.  Secondary endpoints  The secondary endpoints will be as follows:   - Area under the curve of pain over the past 48 hours, assessed every fortnight by a numeric scale from 0 to 100 at 1 year - Functional assessment at 1 year (Quebec scale) - Quality of Life assessment at 1 year (MOS SF-12 questionnaire) - TWIST at 1 year (pain) - Number of days of sick leave between 6 months and 1 year after enrolment |

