**Procedures for minimising missing data**

In order to minimise missing data, all patients will be contacted by phone and/or by email to remind them to send their assessment questionnaire in due course (3 months, 6 months and 12 months after enrolment) and, where necessary, they will be helped to fill in the questionnaire.

Furthermore, it has been demonstrated that offering clinical study patients a symbolic financial compensation improves response rates (Roberts PJ, Torgerson DJ, BMJ 2002). As such, at the end of the study, patients will receive a gift voucher when they have filled in and returned the questionnaires.

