## IV - 3 - REQUIRED NUMBER OF SUBJECTS

The return-to-work rate at 1 year is estimated to be 70% in the control group. The hypothesis is to reach 80% in the intervention group. With a 5% risk and a power of 80%, a total of 600 patients are planned to be enrolled: 300 patients in the short spa therapy group and 300 patients in the control group. Taking into account the risk of loss-to-follow-up, 700 patients will be enrolled.

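### The protocol gives contradictory time origins for follow-up: one section times the questionnaires from enrolment in controls but from the end of spa therapy in the intervention arm

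*Protocol*

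**What the plan says.** Randomisation takes place at the enrolment visit: "After signing ICF1, the patients will be randomised using secure computerised randomisation software" (VII-1). The same section then sets the start of the Month 3, 6 and 12 questionnaires by arm: "from the enrolment visit for the control group and from the end of spa therapy for the intervention group". It also allows "a maximum time period of 3 months between the enrolment visit and the therapy".

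Other parts of the protocol use a single origin:

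- III-4 (Procedures for minimising missing data) has all patients reminded to return their questionnaires "3 months, 6 months and 12 months after enrolment".
- VI-2 defines a secondary endpoint as "Number of days of sick leave between 6 months and 1 year after enrolment".
- IX-1-6 takes changes from the D0 value and runs the pain area under the curve from enrolment to 1 year.
- III-2 gives each patient 12 months of follow-up and the study 36 months, of which 24 are for enrolment.

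The primary endpoint names no origin: "The primary endpoint will be the return-to-work rate at 1 year" (VI-1). Work status is collected on the follow-up questionnaires (VII-3) and compared by a chi-squared test in all randomised patients (IX-1-5).

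**The concern.** A site that follows VII-1 collects different data from a site that follows III-4. Under VII-1 the two arms are observed for different lengths of time after randomisation, and the longer time is always in the spa arm. A chi-squared test on two percentages cannot allow for this. If patients are still going back to work after month 12, the later reading raises the spa rate without any treatment effect.

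There is also a gap. Patients in the spa arm who decline the second consent, or never attend, have no end of therapy. VII-1 gives them no Month 12, yet IX-1-5 analyses them in the spa arm. III-4 expects refusals at a rate no higher than the 10% seen in an earlier spa trial that used the same type of design. At 10% of 350 that is 35 patients.

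A statistical analysis plan, which was not available for this review, could not fully repair this. Pain, function and quality-of-life questionnaires filled in at month 15 do not yield month-12 values.

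**Working it through.** **1. Calendar under VII-1.** A control's Month 12 is 12 months after randomisation. A spa patient's is at most 3 + 12 = 15 months after it, plus the 5-day stay. The last spa patient enrolled, at month 24, could return the final questionnaire at 24 + 3 + 12 = month 39, against a stated study length of 36 months. The 36 months fit only an enrolment origin.

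**2. The plan's own sample size.** Inputs from IV-3 and IX-1-5: "The return-to-work rate at 1 year is estimated to be 70% in the control group", 80% in the spa arm, two-sided 5%, power 80%, 1:1 allocation.

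n per arm = [1.96 √(2 × 0.75 × 0.25) + 0.842 √(0.70 × 0.30 + 0.80 × 0.20)]² / 0.10² = (1.200 + 0.512)² / 0.01 ≈ 293.2, so 294 per arm or 588 in total. The stated 600 is reproduced, and 300 per arm is used below.

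**3. What a lag could do.** The protocol gives no return-to-work curve and no average lag, so both are assumed. There is no true effect, controls are at 70% at month 12, and each arm has 300 complete cases, before any imputation. The spa arm is read at month 12 + x, with the same lag x for every patient. The 1.5 months is the midpoint of 0 to 3; the 3 months is the protocol's maximum.

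- Weibull with shape k: F(t) = 1 − exp[−1.204 (t/12)^k], where 1.204 = −ln 0.30.
- Plateau at 75%: F(t) = 0.75 [1 − exp(−0.2257 t)], where 0.2257 = −ln(1 − 0.70/0.75)/12.

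Worked case, k = 0.5 and x = 3: (15/12)^0.5 = 1.118; 1.204 × 1.118 = 1.346; F = 1 − 0.260 = 74.0%. For the two-sided 5% test against 70%, the critical difference is 1.96 × 0.0367 = 0.0719. The chance of exceeding it in favour of spa is 1 − Φ[(0.0719 − 0.0397)/0.0366] = 1 − Φ(0.88) = 19%.

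| Assumed curve | Lag (months) | Spa rate | Excess (points) | Two-sided rejection |
|---|---|---|---|---|
| Flat at 70% from month 12 | any | 70.0% | 0 | 5% |
| Plateau at 75% | 1.5 | 71.4% | 1.4 | 7% |
| Weibull, k = 0.5 | 1.5 | 72.1% | 2.1 | 9% |
| Plateau at 75% | 3 | 72.5% | 2.5 | 10% |
| Weibull, k = 0.5 | 3 | 74.0% | 4.0 | 19% |
| Constant hazard (k = 1) | 3 | 77.8% | 7.8 | 59% |

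The last row is an upper bound only. I-1 says that the chance of return falls as sick leave lengthens, which is at odds with a constant hazard.

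**4. Effect of the missing-data rule.** IX-3 counts missing primary outcomes as failures in the tested group and as successes in the reference group. Enrolling 700 to keep 600 implies 100 lost; assume 50 per arm. With k = 0.5 and a 3-month lag, spa becomes 0.740 × 300 = 222 of 350 (63.4%) and control becomes 210 + 50 = 260 of 350 (74.3%). Even the constant-hazard case gives about 233 of 350 (66.7%) for spa.

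**5. After the fix.** With one clock there is no timing difference, the test keeps its 5% level, and the sample size does not change.

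**The case against.** The strongest reply is that VII-1 is one sentence against several. Reminders, the sick-leave endpoint, the pain area and the total study length all point to enrolment, so the intention may always have been a common clock. That is a fair case for reading this as a contradiction rather than a deliberate design. It does not remove the problem. VII-1 is the only place that assigns an origin by arm, and it does so where the questionnaires are handed out. The heading of VII-3 also speaks of follow-up after the intervention.

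A reader might infer more than the text supports:

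- **That every spa patient gains 3 months.** Three months is a maximum; no average is given.
- **That the primary result must be biased towards spa.** This needs VII-1 to govern and the proportion at work to be still rising after month 12. VII-3 records professional status, which can reverse with relapse.
- **That the trial would produce false positives at the rates in the table.** Those are complete-case figures. The rule in IX-3, read literally, would put spa below control at the planned loss and make a false positive for spa very unlikely. Its closing words on applying the reverse are unclear. The rule handles missing outcomes only; observed outcomes would still be taken at different times.
- **That the sick-leave window or the fortnightly pain calls shift as well.** VI-2 fixes the window from enrolment, and VII-3 collects sick-leave dates, so it can be computed correctly whenever the form comes back. VII-1 splits only the questionnaires, and IX-1-6 starts the pain area at enrolment.

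**Conclusion.** The contradiction and the missing origin for spa-arm patients who are never treated are facts of the text and need correction whatever the return-to-work curve.

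The bias is conditional. If VII-1 is followed and return to work is still rising, an excess of about 2 points at a 1.5-month lag (k = 0.5), or 2.5 to 4 points at the maximum lag, is a reasonable illustration against a planned effect of 10 points. The matching false-positive rates are about 9%, and 10% to 19%. They rest on an assumed curve, one lag for all spa patients, no true effect and 300 complete cases per arm. If the curve is flat after month 12 the bias is nil. The protocol does not establish that the primary comparison is in fact biased towards spa.

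**What to change.** In VII-1, time all Month 3, 6 and 12 questionnaires from randomisation (D0) in both arms, whether or not spa therapy is received. In VI-1, define the primary endpoint as work status 12 months after randomisation. Align the schedule table in the General outline, III-4, VI-2 and VII-3 with this origin. State once that the sick-leave window and the pain area under the curve run from enrolment, as VI-2 and IX-1-6 already have it.

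The cost is a few sentences and changed mailing dates; the sample size stays as it is. The real downside is that a patient treated late may complete Month 3 close to or before therapy, and Month 12 only about 12 − 3 = 9 months after it. The Month 3 and Month 6 contrasts in the IX-1-6 model would then include some patients not yet, or only just, treated. If results by time since therapy are of interest, they can be given as a descriptive summary in the spa arm.

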## VII - 2 - INTERVENTION PROTOCOL

The patients in the intervention group will receive an intensive spa therapy consisting of the following, on a daily basis for five days (Annex III):

- 2 hours of spa therapy (morning);
- 30 minutes of physical exercises (afternoon);
- 45 minutes of group therapeutic education (afternoon): two sessions dedicated to physical activity and rest (one of which with a CD), two sessions dedicated to work (one of which with a CD) and one pain management session using a CD (45 minutes, all in the afternoon).

They will also receive a guide on lower back pain.

The spa therapy physicians will fill in and send by fax the report of any AEs/SAEs occurring during the therapy to the Clinical Research Unit (URC), at the end of each intervention.

The patients in the control group will receive standard treatment with no restrictions, organised by their referring physicians, general practitioners or specialists, as well as the same guide on lower back pain given to the intervention group.

## VII - 3 - FOLLOW-UP VISITS after the intervention

Patients will undergo follow-up at Months 3, 6 and 12. Follow-up will be done by post or email, depending on the patient’s preference, together with a telephone call if no response is received.

The following data will be evaluated:

- Professional status and return to work;
- Periods of sick leave since the previous visit (dates and number of days of sick leave);
- Assessment of pain over the past 48 hours, assessed using a numeric scale from 0 to 100;
- Lower back pain progress;
- Treatment since the previous visit;
- Adverse events collected;
- Functional indices: Quebec scale;
- Anxiety/Depression: HAD questionnaire;
- Quality of Life: MOS SF-12 questionnaire;
- Fear-avoidance beliefs: FABQ questionnaire (only at the Month 12 assessment);
- Coping strategies: CSQ questionnaire (only at the Month 12 assessment);
- Treatment satisfaction (only at the Month 12 assessment).

Pain over the past 48 hours will also be systematically evaluated once every fortnight by phone (using a numeric scale from 0 to 100). VOICE RESPONSE SYSTEM

## VII - 4 - EXITING THE TRIAL AND EARLY WITHDRAWAL

Patients may leave the study at any time and for any reason, if they decide to do so. This will have no consequences on the quality of any subsequent care that the patient will receive. Patients may also be withdrawn from the trial at the investigator’s discretion. All cases of patients withdrawing from the study must be documented.

For a patient to withdraw from the study early, the investigator must fill in the case report form up to the date of early withdrawal. The reason for the early withdrawal must be specified. Patients withdrawing from the trial cannot be enrolled again in the study. The patient’s treatment will continue in the context of routine care.

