# III – METHODOLOGY

## III - 1 - STUDY TYPE

This is a multi-centre, comparative, randomised, pragmatic, open trial using a modified ZELEN method.

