## IX -1- 5- Primary endpoint analysis

An intention-to-treat analysis will be carried out, i.e., all patients randomised will be analysed in their randomisation arm, regardless of the treatment received and any missing information. The bilateral tests will be carried out at the 5% threshold. The return-to-work rate percentage will be compared using the Chi-squared test.

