## IX -3 - METHOD FOR TAKING INTO ACCOUNT MISSING, UNUSED AND INVALID DATA

In the event of missing data regarding the primary endpoint, the method of maximum bias will be used so as not to favour the hypotheses to be tested. The missing values in the group to be tested will be replaced by failures, while in the reference group, they will be replaced by successful cases, and vice versa.

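### VII-4 provides for no outcome collection after an investigator withdraws a patient, so obtainable 12-month work status can go missing and is then imputed against the spa

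*Protocol*

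**What the plan says.** On withdrawal, VII-4 states: "Patients may also be withdrawn from the trial at the investigator’s discretion". No criteria are given. Withdrawals must be documented with a reason, and on data the instruction is that "the investigator must fill in the case report form up to the date of early withdrawal". The section closes with "The patient’s treatment will continue in the context of routine care". It does not mention outcome follow-up after withdrawal.

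Four other parts of the protocol bear on this:

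- **Design (III-1).** "This is a multi-centre, comparative, randomised, pragmatic, open trial using a modified ZELEN method".
- **Endpoint (VI-1) and its collection (VII-3).** "The primary endpoint will be the return-to-work rate at 1 year". It is collected remotely at months 3, 6 and 12, by post or email, with a telephone call to non-responders. Under VII-1 the patient agrees to this follow-up in ICF1, before randomisation.
- **Analysis set (IX-1-5).** "all patients randomised will be analysed in their randomisation arm, regardless of the treatment received and any missing information".
- **Missing primary outcomes (IX-3).** "The missing values in the group to be tested will be replaced by failures". In the control arm they become successes. The section then adds the converse without explaining it.

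**The concern.** An investigator's decision to end a patient's participation is not the patient's refusal to answer a questionnaire. The month 12 outcome needs no clinic visit and is already covered by a signed consent. If a site does only what VII-4 asks, an obtainable primary outcome becomes a missing one.

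Two features make this matter more here. The trial is open, so whoever withdraws a patient can know the arm. And IX-3 does not treat missing outcomes neutrally: its first-stated direction counts each one against the trial's own hypothesis. Sections I-4 and III-4 set out to keep missing data to a minimum, and VII-4 as worded works against that aim.

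**Working it through.** **Inputs.** Control 70%, spa 80%, 5% risk, 80% power, 300 per arm raised to 700 in total (IV-3); two-sided test (IX-1-5); 350 per arm (Summary); imputation rule (IX-3). The protocol states no rate of investigator withdrawal, so the missing fraction m is an assumption. It is taken as equal in both arms and unrelated to outcome, with no other outcomes missing.

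**Step 1: reproduce the plan's figure.** Pooled two-proportion formula without continuity correction:

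n per arm = [1.96·√(2·0.75·0.25) + 0.8416·√(0.7·0.3 + 0.8·0.2)]² / 0.10² = (1.2002 + 0.5119)² / 0.01 ≈ 293.2, so 294 per arm and 588 in total.

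This agrees with the stated 600. Power is 80.9% at 300 per arm and 86.5% at 350. The step from 600 to 700 implies an allowance of 1 − 600/700 = 14.3% for all losses. That is not an estimate of investigator withdrawals and is not used as one.

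**Step 2: apply IX-3 in its first-stated direction.**

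- Spa rate: 0.8(1 − m)
- Control rate: 0.7(1 − m) + m
- Expected difference: 0.10 − 1.1m, so each 1% missing per arm costs 1.1 points.

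Power in favour of the spa is Φ[(d − 1.96·SE₀)/SE₁], with 350 per arm, SE₀ from the pooled rate and SE₁ from the separate rates. For m = 2%: d = 0.784 − 0.706 = 0.078, SE₀ = 0.03295, SE₁ = 0.03282, and Φ(0.409) = 65.9%.

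| Missing per arm (assumed) | Patients per arm | Difference, points | Power with IX-3 imputation | Power if the same patients are left out |
|---|---|---|---|---|
| 0% | 0 | 10.0 | 86.5% | 86.5% |
| 1% | 3.5 | 8.9 | 77.5% | 86.1% |
| 2% | 7 | 7.8 | 65.9% | 85.8% |
| 3% | 10.5 | 6.7 | 52.7% | 85.5% |
| 5% | 17.5 | 4.5 | 27.2% | 84.7% |

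At 0.5%, about 2 patients per arm, power with imputation is still 82%. The last two columns separate the sources of the loss: the missing patients themselves cost under 2 points of power, and the imputation rule accounts for the rest.

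**Step 3: which way can selective withdrawal push the result?** Equal fractions do not test this, so take each type of patient in turn.

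| Withdrawn patient | True outcome | Scored as | Effect on the spa-control difference |
|---|---|---|---|
| Spa | Failure | Failure | None |
| Spa | Success | Failure | Lowers it |
| Control | Success | Success | None |
| Control | Failure | Success | Lowers it |

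No entry raises the difference. Missingness confined to the spa arm points the same way: at 5% in that arm alone, the rates are 76% v 70%, the difference is 6.0 points and power is 43%.

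**The case against.** Several points on the other side are sound.

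- **VII-4 does not prohibit later collection.** It sets a duty up to withdrawal and is silent afterwards. III-4 plans reminders to all patients but does not say whether withdrawn patients are included. A reader might infer that data must stop; the text supports only that nothing provides for their continuing.
- **The discretion is not unrecorded.** The wording about leaving at any time and for any cause applies to patients who choose to go. Withdrawals must be documented with a reason, and IX-1-3 describes them by group. This makes the losses visible but recovers no outcome.
- **Refusing or stopping the spa is largely covered.** ICF1 covers the year of follow-up and ICF2 only the therapy, III-4 treats refusal as contamination, and IX-1-5 analyses patients whatever treatment they received. The gap mainly concerns patients withdrawn from the trial as a whole.
- **Opportunity may be limited.** The only scheduled investigator visit is at enrolment, and no treatment is prohibited (V-2). The number withdrawn may be small.
- **The power loss belongs mainly to IX-3.** That rule acts on every missing outcome, whatever its cause. The figures cannot be quoted as the effect of VII-4 alone.

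A reader might also infer that an investigator who knows the arm could inflate the spa effect by selective withdrawal. Step 3 shows that the first-stated direction of IX-3 rules this out. Nor is the intention-to-treat analysis broken: every randomised patient stays in it with an assigned value. The defect is that some values would be imputed when they could have been observed.

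**Conclusion.** The point holds as a gap in a conduct rule. VII-4 allows withdrawal at discretion and provides for no outcome collection afterwards, although the primary outcome can be obtained remotely under an existing consent. Followed as written, it loses outcomes that need not be lost. A statistical analysis plan cannot restore data that were never collected.

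The harm is attenuation and loss of power. Its size is conditional: 86.5% falls to about 78%, 66% or 27% if 1%, 2% or 5% per arm are missing and IX-3 is applied in its first-stated direction. These fractions are assumptions; losses from other causes would come on top. The figures also assume that the unexplained converse in IX-3 does not replace the first-stated direction. The point does not extend to patients who themselves withdraw consent to follow-up.

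**What to change.** Amend VII-4 in two respects:

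1. State that a patient withdrawn by the investigator stays in the month 3, 6 and 12 mail and telephone follow-up, at least for the month 12 work status, unless the patient withdraws consent to follow-up.
2. Confirm that refusing or stopping the spa (ICF2) does not end the follow-up agreed in ICF1.

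The cost is a change of protocol wording and a few more questionnaires and calls through the system already in place. No clinical decision changes.
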